| Planned use of linked data (if applicable): Linkage to practice- and patient-level IMD scores is requested to investigate the potential influence of deprivation on any associations found. Both measures are requested to enable sensitivity analyses on the subset with linked patient-level IMD data. Linkage to Hospital Episode Statistics data is requested for a sensitivity analysis using only the 60% of participants with linked data (19), with ethnicity ascertained from HES. Given the higher levels of ethnicity recording in HES than CPRD, this will boost ascertainment of our key exposure up to 80% (18). |
| Definition of the Study population All permanently-registered patients with research-standard data and incident type 2 diabetes Read codes from at least 1 year after 1^st^ January 2006 (start of follow-up; coinciding with when ethnicity was recorded for ≈80% of new registrations (18)) to 31^st^ December 2018 in the CPRD. The study will be restricted to incident cases to enable more precise measurement of treatment stage; people with prevalent type 2 diabetes Read codes prior to 2006 will be excluded.  Type 2 diabetes will be defined by a previously tested algorithm that uses Read codes, medication, blood test results and diabetes-specific process of care Read codes to adjudicate diabetes status (26) – see appendix. Specific exclusions will include: type 1 diabetes, gestational diabetes, non-specified diabetes diagnosed at ≤40 years in Europeans or ≤35 years in South Asians and African Caribbeans (reducing misclassified type 1 diabetes), and secondary diabetes (e.g. drug-induced). |
| Selection of comparison group(s) or controls The UK’s 3 main ethnic groups will be compared, with the following comparisons undertaken for each study sub-question: South Asians versus Europeans, African Caribbeans versus Europeans. Ethnicity will be designated by patient self-report using the 9i% or 9s% Read code hierarchies in CPRD – see appendix for code list. The range of codes will be mapped to the ethnicity codes present in the 2011 UK census (20), with discrepancies or multiple codes being resolved using an algorithm which identifies the most common or most recent codes available (18). For the sensitivity analysis where ethnicity is designated from HES data, usable entries under the “ethnos” code will be collapsed into the 16 ethnicity codes of the UK census. |

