| Data/ Statistical Analysis For all parts of the study, the population will be people with new-onset type 2 diabetes in CPRD from 2006 (see section K, above) and the exposure will be ethnicity (either South Asian vs. European [baseline] or African Caribbean vs. European [baseline], as detailed in section L, above). Covariates in base models will include age and sex, and further covariates will be considered individually, as outlined in section vi) below. Statistical analysis is further considered by objective:   1. **Outcome**: time to initiation of first-line anti-diabetic medication, probability of receiving anti-diabetic 1 year post-diagnosis   **Entry**: date of type 2 diabetes diagnosis  **Exit**: date of first anti-diabetic prescription (defined by the absence of a prescription for the medication in the previous 6 months’ records), or end of study/ leaving CPRD practice/ death  **Analysis**: summary statistics will be compared by ethnicity using Kaplan-Meier time-to-event analysis (cumulative failure probability in a given time frame by ethnicity, comparison of medians by log-rank test), Cox proportional hazards regression models will be used to adjust for confounding/ investigate potential mediators  **Example effect measure**: hazards ratio (HR) for anti-diabetic prescription   1. **Outcome:** proportions of patients prescribed medication from each anti-diabetic (stratified by first- to third-line treatment), antihypertensive and lipid-lowering class (defined by the absence of a prescription for the medication in the previous 6 months’ records)   **Sub-population:** a) all participants starting first- to third-line anti-diabetic treatment, b) all patients on antihypertensives, or c) all patients on lipid-lowering medication  **Analysis:** proportions receiving each drug will be compared by ethnicity, then logistic regression models will be used to adjust for confounding/ investigate potential mediators  **Example effect measures**: odds ratio (OR) of being prescribed metformin (=1) vs. non-metformin medication (=0) at first stage of treatment, OR of being prescribed sulphonylurea (=1) vs. non- sulphonylurea medication (=0) at second stage of treatment, OR of calcium-channel blocking antihypertensive prescription vs. non- calcium-channel blocking antihypertensive in those on antihypertensive treatment, OR of statin prescription vs. non-statin lipid-lowering medication prescription in those with >10% 10 year cardiovascular risk   1. **Outcome:** proportions of patients prescribed each dose of each anti-diabetic, antihypertensive and lipid-lowering medication, stratified by treatment stage (defined by the absence of a prescription for the medication in the previous 6 months’ records)   **Sub-population:** a) all participants on first- to third-line anti-diabetic treatment, b) all patients on antihypertensives, or c) all patients on lipid-lowering medication  **Analysis: :** proportions receiving each dose of each drug will be compared by ethnicity, then logistic regression models will be used to adjust for confounding/ investigate potential mediators  **Example effect measures**: OR of being prescribed maximum dose (2g daily) vs. sub-maximum dose of metformin, OR of being prescribed atorvastatin 10mg per day vs. higher doses (20mg, 40mg or 80mg)   1. **Outcome:** yearly monitoring rate post commencement of medication from each anti-diabetic (first- to third-line), antihypertensive and lipid-lowering class – i.e. number of times HbA1c/ blood pressure/ blood lipids measured per person-year of follow-up, stratified by year after commencement; may be multiple entry dates per person for different medications   **Entry:** first use of any medications of interest from 2006 onwards  **Exit:** first of; end of strata (e.g. 1 year after medication commencement), end of study/ leaving CPRD practice/ death  **Analysis:** summary statistics will be compared by ethnicity, Poisson regression modelling used to adjust for confounding/ investigate potential mediators  **Example effect measures**: yearly monitoring rate ratios (RRs)   1. **Outcome:** time to medication intensification (up-titration, addition or switching) after detection of sub-optimal control of diabetes, hypertension or blood lipids, or probability of intensification 1 year post-detection of sub-optimal control; may be multiple entry dates per person for different medications   **Entry:** date when sub-optimal risk factor control detected (see section M for how this is defined for each risk factor)  **Exit:** first of; date of anti-diabetic, antihypertensive or lipid-lowering treatment intensification, end of study/ leaving CPRD practice/ death  **Analysis:** summary statistics will be compared by ethnicity using Kaplan-Meier time-to-event analysis (cumulative failure probability in a given time frame by ethnicity, comparison by log-rank test), Cox proportional hazards regression models will be used to adjust for confounding/ investigate potential mediators  **Example effect measures**: cumulative failure probability for each ethnic group 1 year post detection of sub-optimal value, comparison of median survival times using the log-rank test by ethnicity, HRs of intensification stratified by year   1. **Outcome:** influence of deprivation, polypharmacy, multi-morbidity, drug adherence (iv) and v) only), patient engagement with healthcare, diabetes duration and HbA1c on any ethnic differences found in i) to v).   **Entry:** as above for i), iv) and v)  **Exit:** as above for i), iv) and v)  **Analysis:** as above for i) to v)  **Covariates:** smoking status, BMI, deprivation, polypharmacy, multi-morbidity, drug adherence, patient engagement with healthcare, diabetes duration and HbA1c  **Effect measures:** we will observe the degree of attenuation of the ethnic difference effect measure for each outcome when each covariate is inserted in turn to models, and thus evaluate the likelihood of confounding or mediation  Sub-group/ sensitivity analyses  Analyses will be stratified by age group, and changes in guidelines and temporal trends in drug usage will be accounted for by stratifying by time.  Three sensitivity analyses will be performed – all to boost ethnicity ascertainment. Firstly, on the 58% of CPRD participants with linked secondary care data from Hospital Episode Statistics (HES) (19), using ethnicity codes from HES - present in 78% (18). Secondly, on new registrants since 2006, 78% of whom have ethnicity codes recorded (19). Thirdly, on patients from practices in the London area; where previous research indicates ethnicity recording to be approaching 60% (28).  Plans for addressing misclassification and bias  ­Plans for addressing misclassification of diabetes status and ethnicity are given above (see sections K and L respectively).  Selection bias may arise in ethnicity recording, i.e. greater recording for patients from ethnic minorities, and may also vary across time (with greater recording after the introduction of incentives in 2004) and geographically (greater in urban areas with more ethnic diversity (28) than rural ones with less). We plan to address this in three ways, as detailed above under the “sub-group/ sensitivity analyses” heading. NB/ we do acknowledge these approaches may in themselves introduce bias, and thus we will carefully compare baseline characteristics between the sensitivity and primary analysis populations.  Though primary care prescription data are almost entirely computerised, bias may be introduced into the descriptive arms of the study from unrecorded prescriptions issued in secondary care; equally medication started in secondary care and continued in primary care may falsely lengthen times to up-titration. We anticipate little bias in the monitoring outcome, where blood tests and clinical data such as blood pressure (including those recorded in secondary care) are generally automatically entered into notes via specific templates. Additionally, some bias may be present regarding the ascertainment of treatment intensification, where the intervention is non-pharmacological or constitutes referral to another service. Therefore we will also search for codes indicating lifestyle modification advice or referral which are chronologically close to the medication exposure period.  We plan to examine the influence of drug adherence in explaining any associations between ethnicity and prescribing, but this will only be measured by proxy using the proportion of days covered method; we are unable to verify whether prescriptions have been obtained from pharmacies or whether medication has been taken.  Multiple comparisons  As the study will involve multiple comparisons, findings will be interpreted with caution, and attention paid to clinically meaningful effect sizes rather than p values per se. |

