| Feasibility counts The primary analysis will be using data from CPRD alone (see section M for sensitivity analyses). Ethnicity recording for active patients is approximately 50% (17, 18). The ethnic breakdown is similar to that of the UK census 2011(20).  From 2000-2017, ≈280K patients initiated first-line and ≈80K second-line treatment for type 2 diabetes in CPRD (8). If 50% of these people had ethnicity codes present in their record, this would correspond to ≈140K starting first-line and ≈40K starting second line treatment. Using the 2011 census to calculate proportions, this would equate to ≈120.4K Europeans, ≈10.5K South Asians and ≈4.6K African Caribbeans initiating first-line treatment and 34.4K, 3.0K and 1.3K respectively starting second-line treatment. These are conservative estimates given the over-representation of ethnic minorities in the diabetic population.  Approximately 77% of the people with diabetes initiating first-line treatments are likely to be on antihypertensives (19), giving numbers for antihypertensive analyses of ≈92.7K Europeans, ≈8.1K South Asians, ≈3.5K African Caribbeans. Previous work in CPRD shows that ≈64% of people with type 2 diabetes receive statins (19), which will yield numbers for the lipid-lowering medication analyses of ≈77.1K Europeans, ≈6.7K South Asians and ≈2.9K African Caribbeans.  For people without diabetes, we expect approximately 219K people to initiate antihypertensive treatment over a similar study period to our own (20), equating to at least 94K Europeans, 6K South Asians and 3K African Caribbeans, once multipliers for ethnicity recording and the 2011 Census ethnicity breakdown are applied. From Chidwick et al (21), 113,035 people over 40 without a prior history of CVD had a high CVD risk score recorded between 2005-2013. Assuming 50% of these people had ethnicity recorded, and proportions by ethnicity are as per the 2011 census, this equates to approximately 49K Europeans, 3K South Asians and 2K African Caribbeans. |

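### The HES sensitivity analysis changes the population and the ethnicity source in one step, so a result that differs from the primary analysis could not be explained

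*Supplement*

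**What the plan says.** The Feasibility counts section of the December 2019 amendment sets the primary analysis: "The primary analysis will be using data from CPRD alone". It puts completeness of the exposure there as follows: "Ethnicity recording for active patients is approximately 50" per cent.

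The section on planned use of linked data in the original application, which the amendment does not restate, describes the HES analysis as "using only the 60% of participants with linked data (19), with ethnicity ascertained from HES". It gives the expected gain as "this will boost ascertainment of our key exposure up to 80" per cent. The sub-group and sensitivity analyses text under Data/Statistical Analysis gives slightly different figures: the analysis is "on the 58% of CPRD participants with linked secondary care data from Hospital Episode Statistics (HES"), with HES codes present in 78%. The amendment carries this text forward by reference, so it is the current plan.

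The section on selection of comparison groups says how HES entries are collapsed to census categories and how multiple CPRD codes are resolved. It gives no rule for combining a CPRD code with a HES code. No run using CPRD ethnicity inside the linked subset is described.

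The plan accepts that its sensitivity analyses could bring bias of their own, and promises to compare baseline characteristics with the primary population.

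**The concern.** The missing-data section names missing ethnicity as its principal worry, rejects multiple imputation and relies on complete cases. It says this is unbiased if missingness is unrelated to outcome given the covariates. The sensitivity analyses are there to probe that condition. The HES analysis is the only one of the three described as using a second source, and so the only one that can classify people whom CPRD leaves unclassified.

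A sensitivity analysis is easiest to read when it changes one thing. This one changes at least two. Suppose the hazard ratio for time to first prescription in South Asian patients differs between the primary and HES analyses. The cause could be any of these:

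- linked patients and practices differ from the rest;
- HES assigns some people to a different group from CPRD;
- people with a CPRD code but no HES code have dropped out;
- people with a HES code but no CPRD code have come in.

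Only the last bears directly on the missing-data question. The authors would have a discrepancy and no planned way to interpret it.

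**Working it through.** **Inputs from the documents.** CPRD ethnicity recording 50% and about 280K first-line initiators (Feasibility counts); linked share 60% and HES completeness up to 80% (planned use of linked data); linked share 58% and HES completeness 78% (sensitivity analyses). The 280K covers 2000-2017 and serves here only as a scale.

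**Assumption.** CPRD recording is also 50% inside the linked subset. The documents do not give that figure.

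**1. The plan's own figure.** 280K x 0.50 = 140K, which matches the stated "this would correspond to ≈140K starting first-line and ≈40K starting second line treatment".

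**2. Completeness within the linked subset.** Missing ethnicity falls from 50% to 100 - 78 = 22%, or 100 - 80 = 20%.

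**3. Whole-cohort yield of HES alone** = linked share x HES completeness.
- 0.58 x 0.78 = 0.452, about 127K of 280K
- 0.60 x 0.80 = 0.480, about 134K of 280K

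HES alone cannot classify more than the 58-60% who are linked, so the 80% can only be a proportion of that subset.

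**4. What changes between analyses.**

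| Analysis | Population | Ethnicity source |
|---|---|---|
| Primary | all CPRD | CPRD |
| HES, as planned | linked only | HES |
| (a) not planned | linked only | CPRD |
| (c) not planned | linked only | CPRD, filled from HES |

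The planned contrast splits as (HES - primary) = [(a) - primary] + [HES - (a)]. The first bracket is the population effect and the second the source effect. Without (a), neither can be obtained.

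**5. Who differs between the sources inside the linked subset** (50% CPRD, 78% HES). Let x be the percentage with both codes. Then CPRD only = 50 - x, HES only = 78 - x, neither = x - 28, so x lies between 28 and 50.

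| | x = 28 | independence, x = 39 | x = 50 |
|---|---|---|---|
| Both | 28% | 39% | 50% |
| CPRD only (lost under HES alone) | 22% | 11% | 0% |
| HES only (gained) | 50% | 39% | 28% |
| Either source | 100% | 89% | 78% |

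Independence check: 1 - (1 - 0.50) x (1 - 0.78) = 0.89. With HES at 80% the combined range is 80% to 100%, and 90% under independence. The documents do not give the overlap.

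**6. Size of run (a).** 0.58 x 0.50 = 29% of the cohort (about 81K of 280K), or 0.60 x 0.50 = 30% (84K).

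**The case against.** The best defence is that HES ethnicity is a separately collected source. The missing-data section fears that poorly engaged patients lack a CPRD code; an exposure that does not depend on GP recording tests whether the result survives. If the results agree, there is little to attribute. This stands as a reason to keep the HES run. It does not help when results differ, and agreement could also hide effects that offset each other.

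The change of population is also acknowledged, and baseline characteristics will be compared. That describes how the populations differ, but not how far an estimate moved because of them. The restriction to new registrants since 2006, with 78% recorded, reaches similar completeness with no stated change of source, and adjustment for prior consultations addresses the named mechanism. Both give useful context but do not separate the two changes in the HES analysis.

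A reader might infer from 45-48% against 50% that the HES analysis defeats its own purpose. The documents do not support that. For complete-case bias the missing fraction in the population analysed matters, and that falls. The plan says openly that only linked participants are used, and the gap lies between rounded literature figures. Nor do the documents rank this as the main check among the three.

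**Conclusion.** The point holds as a matter of interpretability. As written, the HES analysis cannot attribute a discrepancy to the linked population, to HES coding or to newly classified people. Completeness within the subset rises from about 50% to 78-80%, which is worth having, but the figure should not be read as cohort-wide, where HES alone reaches about 45-48%.

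This rests on two things. One is the plain reading that ethnicity in this analysis comes from HES in place of CPRD; the plan never states outright that CPRD codes are set aside. The other is 50% CPRD recording in the linked subset. The 50% describes active patients generally; if recording in a post-2006 incident cohort is higher, the gain within the subset is smaller.

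It is a cheap improvement to one of three sensitivity analyses. Nothing here undermines the primary analysis.

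**What to change.** Within the linked subset, specify three runs of the same model:

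- (a) CPRD ethnicity;
- (b) HES ethnicity, as now planned;
- (c) CPRD ethnicity, filled from HES where missing, with a stated rule for conflicting codes.

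Report CPRD/HES agreement, by ethnic group, among people with both codes. Compare (a) with the full cohort for the population effect, and (c) with (a) for the effect of added ascertainment. Read the second contrast alongside the agreement table: everyone newly classified in (c) carries a HES code, so added ascertainment and HES coding are still mixed unless agreement is shown to be good.

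State that the 78-80% applies within the linked subset, and use one pair of figures in place of 60%/80% in one section and 58%/78% in another.

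Cost: two more runs, (a) and (c), on data already requested, plus one conflict rule and one agreement table.
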